### Cost analysis

The benefits of the proposed interventions must be weighed in the context of the extent to which they can be delivered systematically to large populations. Thus, the logistical barriers and the actual costs of implementation must be determined as part of an assessment of the value of the HIP interventions. Ultimately, the implementation costs of the patient and physician interventions can be compared with each other and with other approaches to improving BP control. Therefore, a cost analysis will be performed to assess the direct costs of implementation, accounting for both fixed and variable costs for start-up and maintenance.

## Discussion

The chronic care model suggests that BP control can be achieved by improving patient self-care and the systems through which care is delivered [29-32]. Patient self-care efforts should be directed at counteracting the effects on BP of obesity, physical inactivity, poor dietary pattern, and non-adherence to prescribed medications [33]. Furthermore, efforts should be made to promote the use of quality improvement systems that can increase physician adherence to established clinical practice guidelines [34,35]. In addition to improving BP control, these approaches can also reduce costs associated with hypertension and its consequences [29]. However, given the resources required to implement such approaches, it is critical that their effectiveness be rigorously established [36].

The Hypertension Improvement Project is a controlled trial to test the separate and combined effects on BP of a behavioral intervention for patients and a quality improvement intervention for physicians. The patient intervention employed proven behavioral methods for promoting healthy lifestyle and adherence to medication regimens. The physician intervention used a quality improvement approach to provide training, motivation, and feedback on performance in a non-threatening way to promote continuous self-improvement and adherence to clinical practice guidelines.

The physician intervention represents a form of quality improvement that can be described as "Facilitated Process Improvement" (FPI) [37]. Similar to CQI, FPI recognizes that a key barrier to implementing systematic improvement programs is provider time: time to become expert in and to apply CQI methodology and time to become familiar with the sorts of interventions that are likely to be effective in a given context. In FPI, several components of the CQI process are delegated to an expert team, with concurrent agreement by providers during education programs. In this case, the team identified the common limiting barriers to optimal outcomes–lack of easy access to guidelines and lack of ongoing feedback regarding conformance to guidelines (the latter issue may be termed "the difficulty of looking over one's own shoulder")–and created tools to address those barriers.

At the time at which this manuscript was prepared, the trial was in progress. All physicians and patients had been enrolled, and experience with the logistical aspects of study conduct had been garnered. There are numerous unique features and lessons gleaned thus far from the conduct of the trial that will set the stage for interpretation of the study results. More importantly, these features and lessons can inform other investigators planning similar studies.

Several of the challenges faced relate to the setting in which the trial is being conducted (Table 6). The study team considered it important to conduct the study in community clinics where such an approach to BP control would ultimately be implemented. Implementation of the HIP trial within a practice-based research network, while innovative, also required attention to issues that are not usually encountered within an academic medical center (AMC). The study required access to work space that was convenient and familiar to participants (i.e., in or near the clinic) but that had minimal impact on clinical care delivery. Not all medical clinics have space for study visits and group intervention sessions. The study team worked closely with clinic staff to schedule study visits on days when clinic rooms were available (e.g., provider day off) and used the waiting room (in the evenings), the clinic conference room, or a nearby facility for the group sessions.

**Table 6 T6:** Study implementation issues

**Challenge**	**Solution**
**Setting**	

Access to clinic space for study visits	Schedule study visits on days when clinic rooms are available.

Access to space for group intervention	Schedule evening sessions; find local facility.

Minimize disruption to practice flow	Study staff responsible for scheduling, check-in, and posting of signage.

Engage clinic staff/communication	Group meeting prior to (and early part) of implementation; use of e-mail; financial compensation to offset practice costs.

Travel to distant sites	Staff coordinate travel together to minimize travel costs.

**Patient population/recruitment**	

Enroll low SES population	Target participants with no insurance, with Medicaid or Medicare without supplemental insurance.

Identify minority population	Target clinics with more minority participants.

Recruit men to participate	Prioritize mailings and phone calls to men.

High proportion of participants at BP goal (clinics are doing well in BP management; volunteer bias)	Chart review to identify patients with uncontrolled BP prior to screening for Cohort 4.

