### Enrollment and randomization of MDs

To avoid contamination among physicians in the same practice, randomization occurred at the level of the practice. Four matched pairs of primary care practices were randomly assigned to physician intervention or control. Practices were matched according to specialty (internal medicine or family practice) and participant mix (percent of participants with Medicaid or Medicare without supplemental insurance). Within each practice, all physicians were invited to participate, with a goal of enrolling 4 physicians at each clinic. All physicians at a given clinic were assigned to the same intervention.

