### Analysis plan

The data cleaning and analysis stage of the HIP trial has begun. The adequacy of randomization will be assessed by comparing the baseline characteristics of the 4 study groups. Chi-square tests will be used for categorical variables, and the analysis of variance will be used for continuous variables.

For the patient intervention groups only, various measures pertaining to adherence to the patient intervention and its impact on intermediate outcomes will be summarized. For example, for each cohort, the number of intervention sessions attended will be summarized. Similarly, changes in weight, diet, and exercise will be tabulated, and whether the mean changes equal zero will be determined.

For the main analysis of BP changes, results by group and cohort will first be summarized, and then tested for a cohort-by-group interaction. If this interaction is non-significant–suggesting that the intervention effects are similar across cohorts–summary results will be reported but will include cohort as a control variable in all models. For the continuous outcome of systolic BP, the main comparison will be derived from an analysis of covariance model that controls for cohort and baseline systolic BP. The primary hypotheses of interest will be the main effect of the patient intervention, the main effect of the physician intervention, and the patient-by-physician interaction. This last interaction assesses, for example, whether the patient and physician interventions have a separate impact on outcome or, alternatively, whether they act synergistically. For the categorical outcome of percentage of patients at goal, a similar strategy will be followed using logistic regression, and these analyses will also be stratified by whether the patient was at goal at baseline.

The analysis plan accounts for the correlations among the responses for individual patients, these correlations being induced by the nesting of time points within patients within physicians within practices. The analysis of variance paradigm will be used, accounting for the correlations among the 3 time points by separately analyzing the paired scores representing differences between baseline and 6 months and between baseline and 18 months. These comparisons can be preceded by a statistical test, such as Hotelling's T^2^, that takes explicit account of these correlations.

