### Sample size and statistical power

The power calculations assumed that the impact of accounting for covariates such as baseline blood pressure (which increases statistical power) and the impact of the clustering inherent to this design (which decreases statistical power) would approximately offset and, thus, that power calculations from the 1-way analysis of variance would apply. If so, having approximately 340 patients complete the study would yield approximately 80% power to detect main effects, although the power to detect an interaction between the physician intervention and patient intervention would be smaller. After accounting for expected drop-outs, the minimum sample size for the primary analysis was set at 400.

Preliminary planning also considered 2 other factors, both of which supported an increase in the sample size above 400, if feasible. First, it was anticipated that the study would analyze various secondary outcome variables, some of which might have effect sizes that were less than 0.3. Second, so that the results could be as generalizable as possible, the study strove to include as many clinics as possible. The design originally intended to include 5 sets of clinics, a number which was also suggested by the fact that the most conservative statistical analysis of the impact of the physician intervention–namely, a sign test that simply counts which clinic out of each pair had the better outcome–would be statistically significant if the physician intervention outperformed the controls at each pair of clinics.

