Other challenges related to the choice of study population. The initial goal was to recruit low-income, ethnic minority participants, who are well-represented in the communities served by the participating clinic network. The study also aimed to comprise a population that was approximately 40% male, as men are often under-represented in lifestyle intervention studies. Because participants were recruited from the practices of enrolled MDs rather than the local community, previously effective targeted recruitment procedures could not be relied upon [38]. However, recruitment was targeted through access to the clinical database serving the participating practices, in which race, insurance, and sex data were available. Enrollment of low-income participants was encouraged by targeting recruitment efforts at patients in the database with no insurance, or with Medicaid or Medicare without supplemental insurance. Patient enrollment demographics were monitored periodically so that subsequent recruitment mailings could be prioritized to ensure a balanced study population. Midway through enrollment, the proportion of men was significantly below goal; in response, mailings and recruitment calls were directed preferentially to men. Despite these efforts, Table 2 indicates that most study participants were at least high school-educated and reported adequate financial resources, and fewer than 40% were men.

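### The primary ANCOVA adjusts only for cohort and baseline SBP, leaving recorded race, sex, age and diabetes out of both the physician and the patient contrast

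*Protocol article*

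**What the plan says.** For systolic BP, the Analysis plan section states that "the main comparison will be derived from an analysis of covariance model that controls for cohort and baseline systolic BP". It names no other covariate for this model, which serves both main effects and their interaction. The same section plans significance tests of baseline characteristics across the four groups, with no adjustment tied to the result. It also says in general terms that nesting of patients within physicians and practices is accounted for.

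On pairing, Enrollment and randomization of MDs says "Practices were matched according to specialty (internal medicine or family practice) and participant mix", where mix means the share on Medicaid or on Medicare without a supplement. Race, sex, age and diabetes are not pairing factors.

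On how each practice's case mix arose:
- Table 1 requires care from a physician who has been randomized.
- Enrollment and randomization of patients says each physician went through the list of hypertensive patients and struck off those thought unsuitable.
- Table 6 gives "Target clinics with more minority participants" as a recruitment measure.
- The Discussion reports: "Midway through enrollment, the proportion of men was significantly below goal; in response, mailings and recruitment calls were directed preferentially to men".

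Table 2 gives a mean age of 60.5 years, 61% female, 37% African-American and 30% with diabetes.

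**The concern.** The physician effect is a comparison of 4 practices with 4. At that number, randomization cannot be relied on to balance patient characteristics that were not pairing factors. Patients also entered after their practice was assigned, and their own physicians screened the list. A difference in case mix between the two practices of a pair could therefore come from selection as well as from chance. Whatever race, sex, age or diabetes predicts about 6-month SBP beyond baseline SBP then sits in the physician contrast.

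Diabetes is the clearest candidate on the document's own terms. Patients with diabetes have a lower BP goal, and the physician feedback reports goal attainment separately for them, so two patients with the same baseline SBP may be managed differently.

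For the patient contrast, individual randomization within clinics handles balance. There the loss is only a slightly wider interval than the collected data allow.

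**Working it through.** **1. The plan's own figure.** The plan states "having approximately 340 patients complete the study would yield approximately 80% power to detect main effects". Planning effect: 0.3 SD, implied by the remark that secondary outcomes include "some of which might have effect sizes that were less than 0.3". Two-sided alpha of 0.05 is assumed, as none is stated. With 170 per level of a factor: 0.3 × √(170/2) = 2.766; 2.766 − 1.960 = 0.806; power = Φ(0.806) = 79.0%. The figure reproduces. 340/0.85 = 400 matches "the minimum sample size for the primary analysis was set at 400" at 15% drop-out. The calculation treats patients as independent, because covariate gain and clustering loss were assumed to cancel: they "would approximately offset and, thus, that power calculations from the 1-way analysis of variance would apply".

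**2. Patient effect.** Patients are randomized within clinics, so the SE scales with √(1 − R²), where R² is the share of residual variance that the four covariates explain. The document gives no R²; 2-8% is assumed.
- R² = 2%: √0.98 = 0.990, SE down 1.0%.
- R² = 8%: √0.92 = 0.959, SE down 4.1%.

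Equivalent extra patients = N × R²/(1 − R²). For the 574 enrolled this is 12 to 50; for 340 completers, 7 to 30.

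**3. Physician effect, race alone.** Assumed: African-American share varying across clinics with SD s = 0.05 to 0.20; SBP difference b = 1 to 4 mm Hg at equal baseline SBP; residual SD 12 to 15 mm Hg; practice ICC 0.01 to 0.05. From the document: 37% prevalence, 8 practices, and 340 completers, so m = 340/8 = 42.5 per practice.

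SD of the shift from chance imbalance = b × s × √(1/4 + 1/4).
- Low end: 1 × 0.05 × 0.707 = 0.04 mm Hg.
- High end: 4 × 0.20 × 0.707 = 0.57 mm Hg, which is 15.7% of a 0.3 SD effect when the SD is 12 (3.6 mm Hg).

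Variance of the effect = (2/4) × [between-clinic variance + within-clinic variance/m]. Most favourable corner (SD 12, b = 4, s = 0.20, ICC 0.01):
- Without race: 0.5 × [1.44 + 142.56/42.5] = 2.397, SE 1.548.
- Race explains 16 × 0.37 × 0.63 = 3.73 in total, of which 16 × 0.04 = 0.64 is between clinics.
- With race: 0.5 × [0.80 + 139.47/42.5] = 2.041, SE 1.429, a fall of 7.7%.

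Over the whole assumed grid the fall runs from 0.0% to 7.7%. At 2 mm Hg it never exceeds 1.9%.

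**4. Physician effect, all four covariates.** Power at 0.3 SD uses noncentral t with 3 df (8 clinics − 4 cohorts − 1). The column headings give the assumed share of between-clinic / within-clinic variance explained.

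| Patients, ICC | None | 5% / 1% | 20% / 5% | 50% / 10% |
|---|---|---|---|---|
| 340, 0.01 | 36.5% | 37.1% | 39.4% | 44.1% |
| 340, 0.05 | 20.1% | 20.7% | 22.8% | 28.8% |
| 574, 0.01 | 47.0% | 48.0% | 51.3% | 58.5% |

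Even at ICC 0, power with 340 completers is 47.4%. The number of practices is the larger limit.

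**5. Why patient level.** Entering a clinic-level share would cost one of the 3 df. At 340 patients, ICC 0.01 and 20% / 5% explained, power is then 29.0%, below the 36.5% with no added covariate.

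**The case against.** The strongest reply is that cohort plus baseline SBP is already a valid ANCOVA. Under practice randomization, chance case-mix differences belong in the error term, and an interval that respects clustering covers them. Much of the recruitment steering is also absorbed by design. Insurance mix was a pairing factor. The push towards men came partway through enrollment, so it falls largely between cohorts. Practices entered two per wave and the plan to cut five sets of clinics to four is described in terms of cohorts, so cohort very probably coincides with matched pair, although this is not stated outright. If it does, the cohort term removes all between-pair differences. All of this stands, and it limits the point to differences within pairs.

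The reply that only precision is at stake is incomplete. Practice randomization does not protect against differences that arise when patients are recruited and screened after assignment. Measured covariates deal with part of that, not all of it.

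A reader might infer from Table 6 that minority share was imbalanced between arms. The document does not support this: the measure was meant to raise the minority share overall, and nothing says it differed within a pair or by arm. Nor does the document show that physicians' screening differed by arm.

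A further objection is timing. Data cleaning and analysis had begun, and the study statistician was not blinded at the DSMB review. Widening the primary model late adds flexibility. This is a fair caution, and it governs who should fix the list.

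**Conclusion.** The point holds as a modest, low-cost improvement to a stated model. Race, sex, age and diabetes are recorded, were not pairing factors and are left out of the primary ANCOVA, so within-pair case-mix differences can remain in the physician contrast and some precision is lost in the patient contrast.

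Size: about 1-4% of the patient-effect SE, and about 0-8% of the physician-effect SE for race alone, near the bottom of that range for most inputs. R², ICC, residual SD, race effect and spread of race across clinics are all assumptions; the document gives none of them.

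Two stronger readings should be resisted. The stated model is not shown to give a biased physician effect. And covariates would not restore the planned 80% power for that effect: with 340 completers, even the most generous assumption in the table reaches only 44.1% at ICC 0.01.

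**What to change.** In the Analysis plan section, add race, sex, age and diabetes as patient-level covariates to the primary ANCOVA, alongside cohort and baseline SBP, for both main effects and the interaction. Do not enter them as clinic-level shares.

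The list should be fixed by investigators still blinded to outcomes, because the study statistician had seen interim results. It should not depend on the planned baseline significance tests. Keep the cohort-plus-baseline-SBP model as a reported sensitivity analysis, so that readers can see what the added covariates change.

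Cost: one sentence in the plan, no new data, a few patient-level degrees of freedom out of several hundred, and a change to the stated model late in the trial, which should be disclosed with its date.

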**Group intervention**	

Finding patients motivated to undergo group intervention	Recruitment by opt-out changed to opt-in/opt-out method.

Attendance	Useful information; mimics real-world implementation.

No individualized counseling (allows implementation in busy setting)	Use community health advisors.

**Physician intervention**	

MD turnover	Refer participants to another participating provider within practice.

Additional work for CPM form completion	Form on non-carbon paper to use as clinic note; brief 1-page form; top part can be filled out by non-MD.

MD time for training module completion	Face-to-face orientation of providers to Web-based (asynchronous) training modules; CME credits offered.

QI developed by researchers (non-practice staff); competing QI initiatives within practice	In future, increase involvement of practice clinicians; use of electronic records to collect BP at routine visits.

Town-gown relationship	Work with existing research partner (PCRC).

BP = blood pressure; CME = continuing medical education; CPM = clinical performance measure; QI = Quality Improvement; JNC = Joint National Committee on Prevention, Evaluation, Detection, and Treatment of High Blood Pressure; MD = physician; PCRC = Primary Care Research Consortium; SES = socioeconomic status.

Even though the study strived to cause minimal disruption to the usual clinic flow, the study team relied on the assistance of clinic personnel to arrange and facilitate several study processes. For example, clinic staff directed participants to the appropriate location for study visits, provided phlebotomy services, distributed blank CPM forms, and collected completed CPM forms. Each of these activities added to the staff's usual responsibilities, but several approaches helped to promote cooperation among study personnel and clinic personnel. First, the study goals and procedures were explained to clinic personnel prior to start-up of a new site. During enrollment and follow-up, the study team maintained frequent and open communication among study coordinators, investigators, and clinic management. Lastly, the study budget included modest compensation to the practices and to the enrolled physicians.

Travel from the AMC to the distant sites (ranging 10–40 miles) was not a trivial issue. The study team tried to travel as a group to minimize costs, and travel expenses were reimbursed. Rising fuel costs during the study affected the budget significantly.

Other challenges related to the choice of study population. The initial goal was to recruit low-income, ethnic minority participants, who are well-represented in the communities served by the participating clinic network. The study also aimed to comprise a population that was approximately 40% male, as men are often under-represented in lifestyle intervention studies. Because participants were recruited from the practices of enrolled MDs rather than the local community, previously effective targeted recruitment procedures could not be relied upon [38]. However, recruitment was targeted through access to the clinical database serving the participating practices, in which race, insurance, and sex data were available. Enrollment of low-income participants was encouraged by targeting recruitment efforts at patients in the database with no insurance, or with Medicaid or Medicare without supplemental insurance. Patient enrollment demographics were monitored periodically so that subsequent recruitment mailings could be prioritized to ensure a balanced study population. Midway through enrollment, the proportion of men was significantly below goal; in response, mailings and recruitment calls were directed preferentially to men. Despite these efforts, Table 2 indicates that most study participants were at least high school-educated and reported adequate financial resources, and fewer than 40% were men.

The patient intervention required weekly attendance at group sessions that lasted up to 2 hours. Several of the clinics served rural areas requiring significant travel by the participants. Some communities were not accustomed to the research activities of AMCs and, thus, patients in those areas may have been less inclined to join a research study for reasons related to lack of trust or information. While these factors mimic challenges to implementation of the patient intervention in real-world settings, they created a greater challenge for recruitment into a research study, especially given that recruitment was based on blind mailings. The initial recruitment letter asked potential participants to call the study team only if they were not interested in participating (an opt-out strategy); if the study team did not receive a response, then a follow-up call was made to answer any questions and determine interest in participating. However, the ratio of calls to enrollees was low, so the recruitment letter was changed to allow patients to also opt in. This option allowed participants to self-select for inclusion, which may have selected more motivated individuals but is still likely to generalize to a real-world implementation of the study intervention, which would ultimately require voluntary participation.

Recruitment of CHAs was somewhat challenging. The initial goal in enlisting CHAs was to recruit people with "natural helper" personalities from the same communities as the target patient population. To that end, flyers were posted in participating clinics, and clinic staffs and community leaders were asked to suggest people from within their communities. The response to this recruitment effort was relatively modest. Although we were able to recruit an adequate number of CHAs for the study with a minimal budget, our selection pool was limited. Future studies incorporating the CHA element may consider including a budget for a greater advertisement effort and other strategies to enhance recruitment.

Challenges involving the physicians were also encountered. A few providers left their participating clinical practices during the course of the 18-month intervention. In this situation, the provider's patients who were enrolled in HIP were referred to another participating provider within the practice. Also, completion of CPM forms often competed with busy and varying clinic schedules, the demands of patient care, or an upcoming review by the Joint Commission on the Accreditation of Healthcare Organizations. To minimize the additional work needed for collecting the CPM data, non-carbon copy paper was used, so that the top portion was used for the clinic note and the bottom portion was used for data entry. This was a brief 1-page form–the top portion was designed so that non-MD personnel (e.g., a triage nurse) could fill out the vital signs and medical history, while the bottom portion was filled out by the provider stating the medication changes and counseling that occurred during the visit. The physician strategy was developed by the study investigators who were not fully aware of all the QI initiatives (ongoing or planned) within the practices. The CPM form, while short and simple, was viewed by the practice staff as an additional form of which to keep track, and they had to modify their usual procedures 1 day a month to collect these data. With the increased use of electronic medical records, future studies should be able to integrate the collection of information about medication changes and counseling within routine charting, although this would also remove a reminder system that might contribute to improved BP management.

Developing the training modules was challenging due to the availability of multiple hypertension guidelines [8,39-41]. The original proposal was written when JNC-6 guidelines were widely used; after the proposal was written and before it was funded, the JNC-7 guidelines were released. The training materials were modified to match the newer version. To promote completion of the modules, they were offered on the internet (allowing providers to complete them when time was available), and providers were given CME credit to provide additional incentive for the time spent.

Overall, implementation of the study within a community setting was facilitated by including the network director ([name]) as part of the study team. The director had worked with the practices and providers on previous studies, and so her pre-existing relationships aided recruitment and troubleshooting of operational issues. Finally, it is important to define rewards and compensation for community practices, not only in terms of financial reimbursement, but also in terms of CME opportunities (categories 1 and 2), acknowledgment in publications, and dissemination of study results.

